### Plans to give access to the full protocol, participant-level data, and statistical code{31c}

On completion of the study, the full protocol, the datasets analyzed during the current study, and the statistical code will be made available to other researchers upon reasonable collaborative request to the corresponding author.

## Oversight and monitoring

### Composition of the coordinating center and trial steering committee {5d}

The coordinating center and steering committee are composed of independent experts and study investigators. They will meet once every 2 months to oversee all aspects of the study and to monitor the safety and progress of the study. ZA will perform the participant recruitment and data collection for the study. All four authors are responsible for the study conduction and final results and reports. When problems occur, they will share information and [name] who is the principal investigator and in charge of supervising the study team, will make the final decisions.

### Composition of the data monitoring committee, its role and reporting structure {21a}

The data monitoring committee will not be formed due to the safety of the evaluation and intervention procedures of the study.

### Adverse event reporting and harms {22}

No mental or physical damage to the participants of this study is anticipated. However, if people are harmed during this study because of evaluations or interventions, this will be reported to the Tehran University of the Medical Sciences ethics committee and the research team of this study, will take responsibility for free treatment.

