In this study, we will be trying to take a more comprehensive look at posture and assess its central aspect using brain data obtained from electroencephalography. Also, another aim of the study will be to investigate and compare the effects of transcortical stimulation and stretching exercises to reduce central complications caused by poor posture, determine the preferred intervention and introduce it for workplaces.

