### Criteria for discontinuing or modifying allocated interventions {11b}

If subjects report seven or higher level of itching, tingling, and heat based on 10-point Likert scale, tDCS will be stopped.

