### Provisions for post-trial care {30}

No mental or physical damage is anticipated due to evaluations or interventions. However, if people are harmed during this study because of evaluations or interventions, this will be reported to the Tehran University of Medical Sciences ethics committee and the research team of this study will take responsibility for free treatment.

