### Data management {19}

At the beginning of the study, participants will be assigned a unique identification code and the data sent to the study assessor will only include the code without participant identification information. Subjective assessments and demographic information collected on paper forms will be entered into specific Excel files and a second study staff member will check the data entry process for accuracy. All paper-based data for the study including consent forms, identifiable information, and questionnaires will be kept separate from each other in a locked cabinet in the motor control laboratory at the School of Rehabilitation of TUMS. The electronic records of the study, i.e., raw data of EEG, Entropy, and the Excel files stored on a password-protected external hard drive and computer. Both paper and digital documents will only be accessible to the research team.

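### Harms are handled only through a cause-conditional report to the ethics committee, so the trial has no like-for-like tolerability comparison to set beside benefit when it names a preferred workplace intervention

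*Protocol article*

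**What the plan says.** Harms are dealt with in two places. Adverse event reporting and harms {22} opens with "No mental or physical damage to the participants of this study is anticipated" and continues that "if people are harmed during this study because of evaluations or interventions, this will be reported". The recipient is the university's ethics committee, and the research team is responsible for free treatment. Provisions for post-trial care {30} gives the same condition: "if people are harmed during this study because of evaluations or interventions, this will be reported to the Tehran University of Medical Sciences ethics committee".

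Criteria for discontinuing or modifying allocated interventions {11b} contains the only tolerability measurement: "If subjects report seven or higher level of itching, tingling, and heat based on 10-point Likert scale, tDCS will be stopped".

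Background and rationale {6a} says that the study will compare the two interventions, then "determine the preferred intervention and introduce it for workplaces". The Discussion adds the hope that results may inform health recommendations for office workers.

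On data and oversight, Data management {19} says "Subjective assessments and demographic information collected on paper forms will be entered into specific Excel files". Item {5d} has a steering committee meet every 2 months, among other things "to monitor the safety and progress of the study". Item {21a} says that no data monitoring committee will be formed.

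**The concern.** To be reported under {22}, an event must count as harm and must also be put down to the study. A complaint that fails either test has no described destination. The protocol nevertheless foresees unpleasant sensations with tDCS, strong enough in some people to need a stopping rule, and it has participants scored on them. Those scores then have no stated role in the results, and no counterpart is described for the other two slump-posture sessions.

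At stake is the recommendation. The second part is a crossover in which each slump-posture participant has tDCS, stretching and no intervention, so it could give a within-person comparison of tolerability, with the no-intervention session supplying the background rate of complaints around 60 minutes of typing. As written, that opportunity is unused, and a preferred workplace intervention could be named without knowing how the two compare on unwanted effects. A report of few or no harms would also be hard to interpret, because the rule counts only events attributed to the study.

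**Working it through.** The protocol states no figure on this point, so the check sets its sections side by side; the arithmetic at the end is illustrative.

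**1. Is there another route for collecting harms?** Items {22} and {30} carry the same cause-conditional rule. No other item describes a definition of an adverse event, questioning of participants, recording by session, or a harms summary.

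**2. Do the sensation scores reach the results?** They appear only in {11b}, as the trigger for stopping. The outcomes in {12} are typing performance, musculoskeletal discomfort, visual analog fatigue, neck kinematics and EEG. Item {19} enters subjective assessments from paper forms, but {12} uses that heading for the discomfort and fatigue scales. Item {20b} plans no additional analyses.

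**3. Can a listed outcome stand in?** Musculoskeletal discomfort is the nearest, and it is compared across the three conditions (Objectives {7}).
- Its body diagram has 3 single regions (neck, upper back, lower back) and 6 left-right pairs (shoulder, forearm, wrist, thigh, knee, lower leg): 3 + 6 × 2 = 15. None is the head or scalp.
- Trial design {8} places all outcome measurements in the first and last 3 minutes of typing. Both interventions come before typing, so what is felt during them is not rated on this scale.

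**4. What happens to a stopped session?** Item {20c} sets aside outcome data arising from non-adherence and does not say whether a stop under {11b} counts as non-adherence. If it does, the outcome data of people who could not tolerate tDCS leave the tDCS condition, and the benefit comparison then describes those who tolerated it. If it does not, this step has no effect.

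**5. What would zero events mean?** The group size is 36 under {14}, or 30 if the six orders are each used five times as {16a} states (6 × 5 = 30). Let p be the true proportion affected and c the fraction of cases captured. Then P(no case recorded) = (1 − p·c)^n. The values p = 10% and c = 100%, 50% and 25% are assumptions with no source in the protocol.

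| Capture c | n = 36 | n = 30 |
|---|---|---|
| 100% | 0.90^36 = 2% | 0.90^30 = 4% |
| 50% | 0.95^36 = 16% | 0.95^30 = 21% |
| 25% | 0.975^36 = 40% | 0.975^30 = 47% |

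With full capture and no events, the one-sided 95% upper limit is 1 − 0.05^(1/n): 8.0% for n = 36 and 9.5% for n = 30. With half capture, the limit for 36 becomes 8.0% / 0.5, about 16%. Under a rule that counts only attributed harm, c is unknown and no such limit can be given.

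**The case against.** The strongest reply is that {22} says reported, not recorded. It fixes what goes to the ethics committee and who provides treatment, and is silent on what is written down. An adverse-event form or stop log is the sort of detail an article leaves to the full protocol. This stands in part: it cannot be said that unattributed events go unrecorded. But the article fills its own harms item with a causality filter, states it twice, and describes nothing beside it. If a fuller document is broader, {22} should be brought into line with it.

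Three stronger readings are tempting and not supported.
- A reader might infer that a stopped session leaves no trace. No section says so: {20c} concerns outcome data, its application to stops is open, and the flow chart and schedule figures are not shown.
- A reader might infer that unblinded staff decide causality. The trial is described as open-label apart from the assessor ({17a}, {17b}), but no section says who makes that judgment.
- A reader might infer that participants are never asked about side effects. The stopping rule presupposes that itching, tingling and heat are rated during tDCS, so the under-capture illustration does not fit those three sensations. It is relevant to effects nobody is described as asking about.

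It is also fair that tolerability is not a stated objective, that {6a} ties the preferred intervention to reducing central complications of poor posture, that the Discussion is hedged, and that each intervention is a single supervised session of about 10 minutes in screened adults. Discomfort after stretching may show on the musculoskeletal scale. These points limit the seriousness. They do not provide a tolerability measure common to the conditions.

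**Conclusion.** The point holds in a limited form. The only described harms provision depends on attribution to the study, the tDCS sensation scores have no stated use beyond stopping stimulation, and no rating common to the three slump-posture sessions covers tDCS effects. The trial therefore has no like-for-like tolerability comparison to weigh against benefit when it names a preferred intervention. Musculoskeletal discomfort fills part of the gap only.

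No efficacy result is shown to be wrong, unless stops count as non-adherence and so remove outcome data. The size rests on assumed rates: the chance of recording no case of a 10% effect runs from 2% to 40% with 36 people and from 4% to 47% with 30, across capture from full to one quarter. The conclusion does not depend on those figures. The change should be made because it is cheap and the stated workplace recommendation needs it. An unseen full protocol could already contain it.

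**What to change.** - Reword {22} so that all adverse events in any session are recorded whatever the suspected cause, with relatedness noted as a separate item. Reporting to the ethics committee can continue alongside.
- Use the same short checklist in all three slump-posture sessions: the {11b} sensations plus skin effect, headache, dizziness, pain and other.
- Keep the {11b} scores and every tDCS stop, with its reason, as study data, and state in {20c} whether a stop counts as non-adherence.
- Report these by condition in one descriptive table, and supply it to the 2-monthly steering meeting.
- Limit any statement of a preferred intervention to what benefit and tolerability together support.

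The cost is about 1-2 minutes per session, one form, one table and a wording change, with no extra visits or staff. Prompting will bring out more minor complaints in every condition, which is why the list must be identical across sessions. No change to the stopping threshold is proposed.

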### Frequency and plans for auditing trial conduct {23}

The project management group will have regular audits to monitor trial-related activities and documents.

### Plans for communicating important protocol amendments to relevant parties (e.g. trial participants, ethical committees) {25}

Any change in the study plan requires the approval of the Ethical Committee.

### Dissemination plans {31a}

All the results obtained from the present research will be published in some articles.

## Discussion

To the best of our knowledge, this is the first study to investigate the impact of poor posture on mental fatigue.

Different techniques have been employed to measure mental fatigue. These methods are classified subjectively, behaviorally, and physiologically [43].

Subjectively, decreased energy [8], alertness [44], or motivation [45] with an increase in feelings of tiredness [8] are the characters of mental fatigue. In this method, standard questionnaires such as F-VAS have been used [43]. Behaviorally, performance deterioration including decreased in accuracy and slower responses, occurs following mental fatigue [9, 10, 46]. Effects of mental fatigue on performance have been studied since the beginning of the nineteenth century; Different theories about cognitive mechanisms have been proposed in this issue. According to these studies, people begin to experience mentally tired and their performance deteriorates when the costs of doing a task overtake the benefits of finishing that task [13]. Performance can be measured in different ways; For employees who are prone to mental fatigue, computer typing provides information about the level of mental fatigue without interfering with regular work activities [13, 47]. Physiologically, mental fatigue is detected by tracking alternations in the neural activity of the cortex [9, 48–50]. EEG spectral band change has been considered a reliable biomarker to detect mental fatigue. Increased slow-band EEG activity (i.e., 4–13 Hz), is associated with decreased mental activity [7].

Recent studies have revealed that mental fatigue has a negative effect on neuromuscular function including strength, muscle activity, and joint steadiness [51]. According to Marcora et al. (2009), during the condition of mental fatigue, people experience greater discomfort, decreased muscle endurance, and a higher perception of effort [46]. These changes in neuromuscular function may lead to loading of the musculoskeletal system and changes in kinematic parameters.

The hypothesis of altered cognitive processing in poor posture has been reported in previous studies although there is a small number of studies on this topic. For instance, better scores of verbal episodic memory was associated with more upright posture, which showed that the cognition of older adults was affected by their posture [52]. With these evidences, it is possible that typing task affects normal and slump posture individuals differently in terms of mental fatigue and kinematic parameters.

In this regard, by comparing tDCS and stretching exercises to monitor the adverse effects of poor posture, we are hopeful that results may contribute towards decision-making for workplaces and may be used as a basis for health recommendations of office workers.

## Trial status

The protocol version is 1.0 (September 21, 2022). Recruitment began on October 1, 2022. We expect that recruitment will be completed on February 5, 2023.

The datasets of study participants are available through the corresponding author upon reasonable request.

## Data Availability

The datasets of study participants are available through the corresponding author upon reasonable request.

## Abbreviations

tDCS: Transcranial direct current stimulation
QEEG: Quantitative electroencephalography
TUMS: Tehran University of Medical Science
VAS: Visual analog scale
CVA: Craniovertebral angle
TKA: Thoracic kyphosis angle
BMI: Body mass index
VDT: Video Display Terminal
FFT: Fast Fourier transform
LSD: Least significant difference
